##### Secondary outcome: Change in quality of life

We will assess the quality of life with the WHO8-EUROHIS questionnaire, originally developed as a part of the European Health Interview Survey (Power, 2003). It consists of four dimensions of quality of life: mental, physical, social and environmental, and it has good internal consistency and acceptability across different countries (Schmidt et al., 2006). Its eight items assess perceived health, energy levels, performance of daily activities, satisfaction with relationships, financial status and living conditions. Respondents answer the questions on a 5-point Likert scale, ranging from ‘not at all’ to ‘completely’, for instance. The mean score is obtained by adding all the item scores and dividing the sum by eight.

##### Secondary outcome: Change in dietary habits

We will evaluate dietary patterns using three-day food records and a 163-item Food Frequency Questionnaire (FFQ). The three-day food recording will utilize the Eat@Work mobile application (Jyräkoski et al., 2023), tailored to keep a reliable food diary with visual and written descriptions of the foods and beverages consumed. We will ask the participants to record their food and beverage intake for one day during the weekend and two weekdays (Thursday to Saturday or Sunday to Tuesday). The food records include the quality and quantity of the consumed foods and beverages, meal timing and additional contextual information. The research nutritionist will review the food records and request clarifying information when necessary. We will calculate the energy and nutrient intakes utilizing the Fineli National Food Composition Database in Finland (Reinivuo, 2014).

The 163-item FFQ is a slightly modified version of the FFQ used in the Kuopio Breast Cancer Study (Männistö et al., 1996), where its validity and reliability have been described. The FFQ was designed to cover the whole diet over the last 3 months. Food items are presented under 13 sub-groups, such as dairy products, grain products, vegetables, fruits and berries. The portion sizes are fixed and specified using natural units (e.g., slice, glass or grams). The FFQ comprises nine frequency options ranging from ‘never’ to ‘six or more times a day’. The average daily food consumption will be calculated by multiplying the consumption frequency by portion size (grams). Average daily energy and nutrient intakes will be calculated using the national food composition (Fineli) database. We will analyse the intake of energy, protein, fats, carbohydrates, fibre, vitamins and minerals.

The Healthy Diet Index (Lindström et al., 2021) will be calculated based on the FFQ data. It includes seven domains: meal pattern, fruit and vegetables, grains, fish and meat, dairy, fats, snacks and treats. Possible scores range from 0 to 100 points, with higher scores indicating better diet quality. It has been shown to correlate with anthropometric measurements, nutrient intakes and metabolic risk factors.

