#### Primary and secondary outcomes

Table 1 presents the primary and secondary outcomes. The outcomes will be assessed utilizing the electronic survey at baseline and after 6 months.

**Table 1. table1-02601060251332358:** Primary and secondary outcomes.

Primary outcome variables	Measurement
Depressive symptoms	CES-D (Radloff, 1977)
Work ability	Current work ability compared with the lifetime best (Tuomi et al., 2007) Three-level work ability indicator (Gould et al., 2015)
Secondary outcome variables	Measurement
Sick leave days related to depressive symptoms	Structured question about sick leave days during the past 6 months
Quality of life	WHO8-EUROHIS (WHO, Power, 2003)
Dietary habits	Food Frequency Questionnaire (Männistö et al., 1996) Healthy Diet Index (HDI; Lindström et al., 2021) Three-day food records Three Factor Eating Questionnaire – 18 (TFEQ-18; Karlsson et al., 2000)
Intervention adherence	Goal Attainment Scaling (GAS; Kiresuk and Sherman, 1968) Level of participation
Intervention acceptability	The Theoretical Framework for Acceptability (TFA; Sekhon et al., 2022)

CES-D: Center for Epidemiological Studies – Depression; TFEQ-18: Three Factor Eating Questionnaire – 18; WHO: World Health Organization.

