##### Acceptability

We will measure the level of intervention acceptability with Sekhon's theoretical framework of acceptability (Sekhon et al., 2022) that delineates acceptability across seven dimensions – affective attitude, burden, ethicality, intervention coherence, opportunity costs, perceived effectiveness and self-efficacy – each accompanied by pertinent questions. We will use the adapted and translated version of the generic questionnaire to measure acceptability and obtain feedback. Table 2 summarizes all the measurements and time points.

**Table 2. table2-02601060251332358:** All measurements and time points.

	Baseline measurements		Final measurements at 6 months		Others
	Electronic survey	Research nurse appointment	Electronic survey	Research nurse appointment	
Background information	X	X			
Health information	X	X	X	X	
Blood pressure		X		X	
Weight		X		X	
Depressive symptoms (CES-D)	X		X		
Work ability (two indicators)	X		X		
Sick leave days	X		X		
Quality of life (WHO8-EUROHIS)	X		X		
Diet quality (Food Frequency Questionnaire)		X		X	
Nutrient intake (3-day food records): Healthy Diet Index (HDI)	X^1^		X^1^		
Eating behaviour (TFEQ-18)	X		X		
Goal attainment (GAS): During the intervention					X
Intervention adherence (during the intervention)					X
Acceptability (TFA)			X		

CES-D: Center for Epidemiological Studies – Depression; GAS: Goal Attainment Scaling; TFA: Theoretical Framework of Acceptability; TFEQ-18: Three Factor Eating Questionnaire – 18; WHO8-EUROHIS: World Health Organization EUROHIS.

^1^
Eat@Work mobile app.

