#### Individual counselling

The main contribution of the intervention is the individually tailored nutrition counselling provided to each participant by the same research nutritionist. The focus is on the personal goal towards the adoption of the recommended diet by participants through personalized goal setting. The first individual counselling session lasts 1–1.5 h. During the first session (Table 3), the nutritionist evaluates the participant's background factors, dietary habits, nutrient intake and eating behaviour. The participant sets adequate goals and means to achieve them with the nutritionist. The framework is the GAS method (Kiresuk and Sherman, 1968). Goals and means will be written in the personal nutrition plan. During the second individual meeting (1 h), the achievement of the goals will be assessed using the GAS method (Kiresuk and Sherman, 1968) and potential challenges and solutions will be discussed by applying the principles of motivational interviewing (Miller, 1996).

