One limitation is the lack of blinding of the participants and study staff in this type of intervention. However, this is unlikely to cause bias for the investigators, as the data come from questionnaires completed by the participants and because the intervention provider will not analyse the data. The second limitation concerns the issues related to the questionnaires, such as temporal variability and treatment expectations that can influence the responses. However, we will use validated questionnaires to minimize these issues. The third potential limitation is that subjects randomized to the control group might withdraw from the study. We try to reduce the risk by offering them one nutrition counselling session, feedback on their food records and a personal nutrition plan after the intervention. The fourth possible limitation is that the participants in both groups may modify their eating habits because they are aware of being observed, the phenomenon known as the Hawthorne effect (Sedgwick and Greenwood, 2015). Moreover, participants in the intervention and control groups may have different treatment expectancies that can influence their behavioural and self-reported outcomes.

This study will provide novel evidence of the effectiveness of nutrition counselling on depressive symptoms among mental health and substance abuse professionals. Based on the acquired knowledge, prevention programmes can be implemented for the targeted population to sustain their mental health, quality of life and work ability.

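### The reasons given for expecting no investigator bias do not cover the three-day food records, which the unblinded research nutritionist reviews and queries before nutrient intake is calculated

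*Protocol article*

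**What the plan says.** Four parts of the protocol article bear on this point.

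- **Handling of the food records** (Secondary outcome: Change in dietary habits). Participants keep a three-day record in a mobile application. Then: "The research nutritionist will review the food records and request clarifying information when necessary". The next step is: "We will calculate the energy and nutrient intakes utilizing the Fineli National Food Composition Database in Finland".
- **Delivery of the intervention** (Individual counselling). The main component is "individually tailored nutrition counselling provided to each participant by the same research nutritionist". In the first session "the nutritionist evaluates the participant's background factors, dietary habits, nutrient intake and eating behaviour"; goals are set with the participant and their attainment is assessed in the second session.
- **Status of the records.** Table 1 lists them under the secondary outcome of dietary habits ("Three-day food records Three Factor Eating Questionnaire – 18"). Table 2 has a row beginning "Nutrient intake (3-day food records", marked at baseline and at 6 months.
- **Blinding** (Summary, first limitation). Lack of blinding of participants and study staff is acknowledged, but "this is unlikely to cause bias for the investigators, as the data come from questionnaires completed by the participants". A second reason follows: the person providing the intervention does not analyse the data. The Statistical analyses section adds that a statistician from outside the study does the analysis.

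**The concern.** The Summary offers its reassurance for the trial's data as a whole and makes no exception. The food records do not fit the description on which it rests. A staff member reads each record, judges whether it needs clarifying and can ask the participant for more before intake is computed. At 6 months that person is unblinded and, on the natural reading, has counselled the intervention participants and helped to set their dietary goals.

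If the number or kind of queries differs between arms, the recorded intake can differ between arms for a reason other than what people ate. Dietary change is the trial's evidence on whether the counselling altered diet at all, so a distorted intake result could mislead the interpretation of a depressive-symptom result in either direction.

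**Working it through.** No arithmetic applies: the point concerns who handles the data, when, and with what knowledge. The check is whether each stated safeguard reaches the food records.

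1. **Does the first reason (participant-completed questionnaires) reach them?** Only in part. Participants make the entries, but the dataset used for intake is the record after staff review and any clarification. The order in the text is record, review and query, then conversion through the food composition database. A staff step therefore lies between the participant and the outcome value.

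2. **Does the second reason (the provider does not analyse) reach them?** No. It protects the analysis stage, as does the outside statistician. Neither can detect or undo a difference that entered while records were being clarified.

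3. **Is the reviewer unblinded?** Yes, on the Summary's own statement about study staff. No masked review of the 6-month records is described.

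4. **Is the reviewer also the counsellor?** This is an inference. The dietary-habits section speaks of the research nutritionist, with the definite article. The counselling section uses the same title and says it is one and the same person for every participant. Nothing mentions a second nutritionist. Step 3 does not depend on this inference; it only makes the exposure stronger, because the counsellor also knows the participant's goals and earlier diet.

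5. **At which visit?** The Randomization section places allocation after the baseline measurements, so the baseline records are largely safe. The article does not say whether the review and querying of those records also finish before allocation. The main exposure is the 6-month review.

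6. **Which outcomes?**
   - The CES-D and both work ability indicators come from the electronic survey and are not touched.
   - The food frequency questionnaire has its own route to intake ("Average daily energy and nutrient intakes will be calculated using the national food composition (Fineli) database"), with no nutritionist review stated.
   - The text bases the Healthy Diet Index on that questionnaire. Table 2 prints the index in the food-record row instead; I follow the text.
   - What remains exposed is energy and nutrient intake from the food records.

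**The case against.** The strongest reply has four parts.

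- **The article claims little.** It says bias is unlikely, not impossible, and lists lack of blinding as a limitation in the same paragraph. This stands. A reader might infer that the claim is simply untrue, or that the nutrient results will be biased in favour of counselling. The documents support neither. They show only that the stated reasons do not cover this outcome. Queries could as easily recover omitted snacks as omitted vegetables, and the visual and written descriptions in the records limit how far a reviewer can move them.
- **The reviewer and the counsellor may be two people.** This is possible, since their identity is inferred. The reviewer would still be unblinded staff, so the first reason would still not reach the records.
- **A query rule is working-instruction detail that an article leaves out.** This is fair: one may exist, and its absence from the article is not the finding. The finding is that the reassurance, as worded, conflicts with the procedure, as worded.
- **The reach is narrow.** This is also right. It is one instrument within one secondary outcome, and participants' own expectations in self-report, which the Summary acknowledges, may be the larger threat. The fix does not remove that threat. It does remove a separate one that can be avoided cheaply.

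**Conclusion.** The point holds in limited form. The two reasons in the Summary do not extend to nutrient intake from the three-day food records, because an unblinded staff member may query those records before intake is calculated. The exposure is mainly at 6 months. The primary outcomes are unaffected, and no such review is stated for the food frequency questionnaire.

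Neither the direction nor the size of any bias can be derived from the article. One could assume a shift between arms and compute how often a null comparison would then be declared positive, but that would show only what the assumption implies, so I give no figure.

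The conclusion rests on two readings: that study staff in the Summary includes the record reviewer, and that no masked review exists elsewhere. That the reviewer is also the counsellor is the natural reading but is not needed for the conclusion. This is a worthwhile, inexpensive improvement and not a threat to the trial's main result.

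**What to change.** Keep the same staff and change the procedure:

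1. Complete the review of the baseline records before allocation is revealed.
2. Present the 6-month records for review under a study code, without name, arm or counselling notes.
3. Apply one fixed query checklist to every record in both arms, for example missing portion size, missing meal or missing drink.
4. Send queries through the mobile application or the research nurse, allow one round, and lock the record before nutrients are calculated.
5. Limit the Summary statement to the self-completed questionnaires and name the food records as the exception.

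If the reviewer and the counsellor are in fact different people, say so; steps 2 to 4 remain useful because the staff are unblinded.

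**Cost:** a short working instruction, a coded export and one revised sentence. Records would receive slightly less individual clarification, and masking would be incomplete where the reviewer recognises a participant's diet. The fixed checklist still limits discretion in that case.

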##### Secondary outcome: Change in eating behaviour

We will assess eating behaviour with the Three Factor Eating Questionnaire – 18 (Karlsson et al., 2000). Its 18 questions measure three domains of eating behaviour: emotional eating, uncontrolled eating and cognitive restraint. There is substantial evidence of a positive correlation between higher emotional eating and depressive symptoms (Dakanalis et al., 2023), and the two other subscales also have associations with depressive symptoms (Paans et al., 2018; Rachubińska et al., 2024). Responses to 17 questions are on a 4-point Likert scale, and one response is on an 8-point continuous scale. The total scores of each dimension are calculated by a formula that gives the total scores between 0 and 100 (The Finnish Association for the Study of Obesity, 2024).

##### Secondary outcomes: Intervention adherence and acceptability

We will measure intervention adherence with Goal Attainment Scaling (GAS; Kiresuk and Sherman, 1968) and the number of sessions attended during the intervention. Level of participation is the most common way of measuring adherence in psychological therapy, behavioural change and rehabilitation interventions (Giovanazzi et al., 2022). With the GAS method, participants will set goals and evaluate their achievements during individual sessions. The GAS method has been used in various healthcare interventions, and its purpose is an orientation towards participant-centred care, meaning that the focus is on what matters most to the participant (Logan et al., 2022). The goals are weighted and assigned on a 5-point scale, 0 meaning the expected, realistic outcome, +1 and +2 better than expected and −1 and −2 worse than expected outcomes. We will use a formula to calculate a T score on the attainment level of the goals (Logan et al., 2022).

##### Acceptability

We will measure the level of intervention acceptability with Sekhon's theoretical framework of acceptability (Sekhon et al., 2022) that delineates acceptability across seven dimensions – affective attitude, burden, ethicality, intervention coherence, opportunity costs, perceived effectiveness and self-efficacy – each accompanied by pertinent questions. We will use the adapted and translated version of the generic questionnaire to measure acceptability and obtain feedback. Table 2 summarizes all the measurements and time points.

**Table 2. table2-02601060251332358:** All measurements and time points.

	Baseline measurements		Final measurements at 6 months		Others
	Electronic survey	Research nurse appointment	Electronic survey	Research nurse appointment	
Background information	X	X			
Health information	X	X	X	X	
Blood pressure		X		X	
Weight		X		X	
Depressive symptoms (CES-D)	X		X		
Work ability (two indicators)	X		X		
Sick leave days	X		X		
Quality of life (WHO8-EUROHIS)	X		X		
Diet quality (Food Frequency Questionnaire)		X		X	
Nutrient intake (3-day food records): Healthy Diet Index (HDI)	X^1^		X^1^		
Eating behaviour (TFEQ-18)	X		X		
Goal attainment (GAS): During the intervention					X
Intervention adherence (during the intervention)					X
Acceptability (TFA)			X		

CES-D: Center for Epidemiological Studies – Depression; GAS: Goal Attainment Scaling; TFA: Theoretical Framework of Acceptability; TFEQ-18: Three Factor Eating Questionnaire – 18; WHO8-EUROHIS: World Health Organization EUROHIS.

^1^
Eat@Work mobile app.

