#### Sample size calculation

We calculated the sample size based on the expected change in depressive symptoms, measured with the CES-D scale (Radloff, 1977). We expect depressive symptoms to decrease in the intervention group from 14 to 9.9 points (Katsuta et al., 2021; Konttinen et al., 2010; Mondal et al., 2022) and assume that depressive symptoms will not change in the control group. The calculation is based on an estimated power of 0.8 with an expected dropout rate of 25%. The calculated sample size was 125, meaning 62 or 63 participants per group (ß = 0.2, a 0.05).

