### Intervention

Subjects in the intervention group participate in a 6-month multifactorial, tailored nutritional counselling consisting of two individual sessions with a personal nutrition plan described below and three group counselling sessions in smaller groups with 15–20 individuals. Combining individual and group counselling allows participants to meet their personal needs, set individual goals and receive peer support. The sessions are held monthly at participants’ workplaces or at the university. Table 3 presents the themes and content of the sessions in chronological order. The principles of nutrition counselling are based on the Finnish Nutrition recommendations (Finnish National Nutrition Council and Finnish Institute for Health and Welfare, 2024). We will advise the participants on the following while taking into consideration their individual needs:
1.Vegetables, fruit and berries: at least 500–800 g daily in total2.Whole grain products: at least 90 g daily, meaning, for example, three slices of bread, one portion of oatmeal and one decilitre of cooked barley groats3.Unsweetened, fat-free or low-fat dairy products: 350–500 mL daily4.Non-tropical vegetable oils and vegetable-oil-based margarine: at least 25 g daily, avoiding butter and tropical oils5.Fish: 300–450 g weekly, including at least 200 g of fatty fish6.Pulses and legumes: 50–100 g (cooked), to replace meat and poultry, at least partly7.Red meat: maximum of 350 g (cooked) weekly and avoidance of processed meat8.Maximum of one egg daily9.Water is the main drink10.Added sugar as little as possible (maximum of 10% of energy intake)

**Table 3. table3-02601060251332358:** Content of the nutrition counselling sessions.

	Theoretical framework	Content	Session and home assignments
**1^st^ individual session:** Personal nutrition plan	Goal attainment scaling (GAS; Kiresuk and Sherman, 1968)	Evaluation and feedback on the participants’ diet	Personal goal setting
**1^st^ group session:** Everyday life and meal frequency	Psychoeducation	Introduction theme: Diet and depression Theme: Importance of regular meal frequency	Daily factors associated with own mental well-being Home: Test of dietary habits

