**2^nd^ group session:** Good food, better mood	Peer support (Lim et al., 2021) Mindful eating (Nelson, 2017)	Notes of dietary habits: pros and cons Theme: Health-promoting diet, topic requests of the participants Mindful eating activity	Home: Adding a mind-friendly food item to one's diet Home: Daily life lists of futilities, successes and reasons for gratitude
**2^nd^ individual session:** Goal attainment and further plan	GAS (Kiresuk and Sherman, 1968) Motivational interviewing (Miller, 1996)	Discussion about goal attainment, motivation and challenges	Evaluation of goal attainment
**3^rd^ group session:** Hope for the future	Psychology of long-term lifestyle changes (Teixeira et al., 2015)	Theme: Successful eating regulation skills	Successes during the intervention

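### Acceptability is asked only once, in the 6-month survey, so intervention participants who withdraw earlier may have no score and reported acceptability may be too favourable

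*Protocol article*

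**What the plan says.** The Acceptability section names the instrument, "We will use the adapted and translated version of the generic questionnaire to measure acceptability and obtain feedback", and lists seven dimensions, among them burden, opportunity costs and affective attitude. That sentence gives no time point. The timing comes from Table 2, whose caption says that it covers every measurement and its time. The row for acceptability has a single mark, under the electronic survey at 6 months. Table 2 also has a column for measures taken at other times. It is used for goal attainment and adherence during the intervention, but not for acceptability.

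Adherence has two measures: Goal Attainment Scaling and the number of sessions attended. On the first, the section on intervention adherence and acceptability says: "With the GAS method, participants will set goals and evaluate their achievements during individual sessions". There are two individual sessions. Goals are set at the first, and the section on individual counselling places the rating at the second: "During the second individual meeting (1 h), the achievement of the goals will be assessed using the GAS method". The Intervention section adds: "Table 3 presents the themes and content of the sessions in chronological order". In that order the second individual session is the fourth of five.

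The sample size section allows for loss, "with an expected dropout rate of 25" per cent, without splitting it by arm or by time of leaving. The total is 125, or 62 or 63 per group.

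**The concern.** Acceptability asks participants how they judged the programme. A person who finds it burdensome or too costly in time is more likely than others to withdraw, and under the stated schedule may never be asked. The missing scores may therefore depend on the very thing being measured. Sessions attended would show that people left, but not how they judged the programme, and the article describes no other acceptability measure.

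An analysis plan can say how missing scores are handled, but it cannot recover answers that were never requested. What is at stake is whether the reported figure describes everyone offered the programme or only those still responding at 6 months. The former is what anyone considering wider use would want to know.

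Goal attainment has a milder form of the same problem. Someone who stops before the second individual session, or misses it, has goals but no rating.

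**Working it through.** **Inputs from the protocol article.** Total 125, allocation 1:1, dropout 25% (Sample size calculation, Randomization); acceptability once, in the 6-month electronic survey (Table 2).

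**The plan's own figure.** The expected CES-D difference is 14 − 9.9 = 4.1 points, with power 0.8 and alpha 0.05. The article gives no standard deviation, so 125 cannot be rebuilt from its stated inputs alone. With a two-sided test and division by 0.75 for loss, a standard deviation of 7.0 gives 123 in total and 7.1 gives 128. The figure is therefore compatible with about 7.1. Nothing below depends on this; only the arm size and the 25% are used.

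**Does the 25% apply to acceptability?** The dropout allowance belongs to the CES-D calculation. Table 2 collects the final CES-D in the same 6-month electronic survey as acceptability, so a participant lost to one is normally lost to the other. Someone who stops counselling but still answers the survey is not among the 25%.

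**Number unscored, equal loss by arm (assumption).**
- 62 × 0.25 = 15.5 and 63 × 0.25 = 15.75, so about 16 without a score.
- 62 × 0.75 = 46.5 and 63 × 0.75 = 47.25, so about 47 with one.

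**Bias.** For any score or proportion, bias of the scored-only result = share unscored × (mean in scored − mean in unscored). The article defines no proportion rating the programme acceptable, so the percentages here are illustrations and not its endpoint.

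| Assumed gap, scored minus unscored (percentage points) | Bias at 25% unscored | Bias at 10% unscored |
|---|---|---|
| −20 | −5 | −2 |
| 0 | 0 | 0 |
| 20 | 5 | 2 |
| 40 | 10 | 4 |
| 60 | 15 | 6 |

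The 10% column stands for losses that fall mainly in the control arm. With about 62.5 per arm, overall loss is 0.25 × 125 = 31.25. If the intervention arm loses 6.25, the control arm loses 25, which is 25/62.5 = 40%.

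**Against sampling error.** Suppose 80% of those scored find the programme acceptable (assumption).
- At 25% loss the standard error is √(0.8 × 0.2 / 47) = 0.058. The bias reaches one standard error when the gap is 0.058/0.25, about 23 points.
- At 10% loss, with 56 scored, it is √(0.8 × 0.2 / 56) = 0.053, and the gap needed is about 53 points.

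**Limits without any assumption about leavers.** At 25% unscored, an observed 80% is compatible with 0.75 × 80 = 60% (no leaver finds it acceptable) up to 60 + 25 = 85% (all do) in the whole arm.

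**Goal attainment.** The order in Table 3 is first individual, first group, second group, second individual, third group. The unrated are those who leave before, or miss, the fourth session. The article does not give that share, so no figure is calculated.

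**The case against.** The strongest reply is that this is ordinary attrition. Every 6-month outcome, including the primary one, is missing for people lost to follow-up. Asking about acceptability at the end is also a coherent choice, because perceived effectiveness and opportunity costs are best judged after the programme, and goals can be rated only after time to pursue them. The article is condensed, and withdrawal procedures or missing-data rules may sit in documents not shown.

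Much of this stands. The end-of-programme form should stay, and the absence of a missing-data rule is no finding. It does not remove the point, because the single time point is a stated schedule and not an omission, and unlike CES-D this construct overlaps with the reasons for leaving.

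Four stronger readings are tempting and are not supported:
- *Leavers cannot be scored.* The questionnaire is part of the 6-month survey, not of a counselling session. The analyses follow intention to treat, and nothing excludes people who stopped attending from that survey. Those who leave after the second individual session already have a goal rating.
- *Both secondary outcomes will come out too favourable.* The direction depends on how leavers would have answered. Adherence also has sessions attended, which covers everyone and would show poor attendance.
- *A quarter of the arm will lack a goal rating.* The 25% is not tied to the fourth session, and the outcome is a weighted T score, so a raw mean on the five-point scale does not represent it.
- *Roll-out will rest on the acceptability scores.* The Summary says only that prevention programmes can follow from the knowledge gained, directly after a sentence about effectiveness on depressive symptoms.

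The withdrawal risk that the Summary discusses is in the control arm, so intervention losses may be well below 25%.

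**Conclusion.** The point holds in a limited form. Acceptability is scheduled once, at 6 months, so intervention participants who withdraw earlier may be unscored: about 16 of 62 or 63 if the planned dropout is equal by arm. An upward bias is plausible, and probable if burden, opportunity costs or dislike of the programme drive leaving, but it is not demonstrated. At the planned loss it is a quarter of the difference between scored and unscored participants. Under the illustrative gaps of 20 to 60 percentage points it is large enough to matter at 25% loss and modest at 10%.

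The goal-attainment T score describes only the participants who were rated. That limits its interpretation and is not an error in the design. All of this concerns descriptive secondary outcomes in the intervention arm.

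**What to change.** Add a second trigger to the acceptability row of Table 2: send the same electronic form to an intervention participant when that person withdraws. Keep the 6-month form for everyone else, including those who stopped attending counselling but remain in the trial. Show leavers' answers separately from those given at 6 months.

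The cost is small: one more trigger for an existing form and one more reported line, with no extra visits. The downside is that some leavers will not reply, and those who do will answer at a different point in the programme, so the two sets should not be pooled without comment.

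Goal attainment needs no change in collection. Report its T score as a result among those rated, beside the number of sessions attended. Further choices, such as how unrated goals enter a sensitivity analysis, belong in the analysis plan.
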